
#### Model evaluation and validation

These models are going to be evaluated within a nested cross-validation framework, with inner loops for hyperparameter tuning and outer loops for performance estimation, to ensure an unbiased assessment of generalisation performance. All transformations, feature-selection procedures, class-balancing strategies and hyperparameter optimisation steps are going to be confined to the training folds and then applied to the corresponding validation/test folds. For RF models, predictive performance will also be assessed using the out-of-bag (OOB) error rate, which provides an internal estimate of generalisation performance without the need for a separate validation set. OOB misclassification rates and class-specific OOB errors are going to be examined as global and category-specific performance indicators. For models evaluated using cross-validation, performance is going to be quantified using a combination of metrics, including balanced accuracy, sensitivity, specificity, positive and negative predictive values and area under the receiver operating characteristic curve (AUC), allowing comparison across algorithms in the presence of class imbalance.

This multi-step modelling strategy was designed to balance predictive performance, robustness and interpretability in the context of a complex, high-dimensional biomarker dataset. Because the final model specification depends on the observed data structure and on the retained feature set, the complete algorithmic configuration, selected hyperparameters and final validation results are going to be reported in the subsequent results manuscript. A schematic overview of the machine-learning pipeline, including preprocessing, feature selection, model training, validation and performance evaluation, is provided in Figure 3. This workflow illustrates the sequential and nested structure of the analysis and highlights the measures adopted to minimise overfitting and information leakage.

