### Sample size calculation

In the absence of a reliable biomarker for predicting the response to antimigraine drugs, we considered, on an empirical basis supported by the limited available data, the difference in baseline methylation levels of CpG islands of the RAMP1 gene, a key receptor subunit of calcitonin gene-related peptide (CGRP), between migraine subjects who are responders and those who are non-responders to CGRP-targeting mABs.

The minimum sample size was inferred considering previous exploratory epigenome-wide association scans (EWAS) in migraine. Wan D. et al. (16) found that the methylation level of CpG islands of the RAMP1 gene, a key receptor subunit of CGRP, was significantly lower in females living with migraine than in healthy female volunteers (2.18% ± 1.91% vs. 5.85% ± 5.41%). Taking this variance into account, we computed a sample size of 47 participants per group (80% power, 5% significance level). Moreover, we considered a 6% loss of participants. Given the rate of >75% response to erenumab observed in randomised clinical trials (30%), as well as the rate of <25% response, we required a minimum sample size of 168 subjects with migraine at baseline and 51 controls.

This sample-size calculation was designed to support the proof-of-concept biomarker-discovery component of the study and was not intended to provide statistical power for definitive high-dimensional machine-learning model development. Therefore, machine-learning analyses are considered exploratory and hypothesis-generating, with the aim of reducing dimensionality and prioritising candidate multimodal predictors for future validation in larger independent cohorts.

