#### Machine learning

##### Preprocessing and feature selection

Given the multimodal nature of the BIOMIGA dataset and the high dimensionality arising from the integration of clinical, psychometric, biomolecular, genetic, epigenetic and neuroimaging variables, a structured preprocessing and feature-selection pipeline are going to be implemented to reduce dimensionality, limit multicollinearity and minimise the risk of overfitting.

Continuous variables are going to be inspected for distributional properties and standardised when appropriate. Categorical variables are going to be encoded using dummy variables. Pairwise correlation analysis is going to be performed to identify highly collinear features, and redundant variables will be excluded before model training.

An initial univariate feature-screening step is going to be applied to reduce the feature space. Candidate predictors is going to be tested for their association with the target variable (treatment response category) using appropriate statistical tests (*t*-test or ANOVA for continuous variables; *χ*^2^ test for categorical variables). Variables not showing evidence of association is going to be excluded from subsequent modelling. This step is going to be used exclusively for dimensionality reduction and not for inferential purposes.

To prevent information leakage, all preprocessing and feature-selection steps is going to be performed within the training data only, following best practices for predictive modelling. Given the protocol-oriented nature of the present manuscript and the proof-of-concept design of BIOMIGA, the machine-learning analyses are planned as an exploratory predictive modelling component intended to generate and prioritise candidate multimodal predictors of treatment response, rather than to provide a definitive externally validated clinical prediction tool.

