##### Machine learning (ML) algorithms

As the primary modelling approach, RF classification was selected because it is well suited to high-dimensional biomedical datasets, can model non-linear relationships and interactions among predictors, and provides internal estimates of generalisation error through out-of-bag (OOB) samples. RF models is going to be trained using bootstrap aggregation, with random feature selection at each node split. Hyperparameter tuning will consider the number of trees, the number of variables sampled at each split, tree depth and terminal node size; final values are going to be selected according to cross-validated/OOB performance. RF-derived feature-importance measures are going to be used to rank predictors according to their contribution to classification performance. This approach is consistent with recent migraine studies using ML to predict response to anti-CGRP monoclonal antibodies (26, 28).

To assess the incremental predictive value of multimodal data integration, RF models are going to be developed using a progressive feature expansion strategy. Models are going to be trained and compared using: (i) clinical and biochemical variables; (ii) clinical, biochemical, and genetic variables; (iii) clinical, biochemical, genetic, and epigenetic variables; (iv) clinical, biochemical, genetic, epigenetic, and structural MRI variables; and (v) the full multimodal dataset including clinical, biochemical, genetic, epigenetic, structural MRI, and functional MRI (fMRI) features. This sequential approach will quantify the added predictive contribution of each data modality and reduce the likelihood that model performance is driven by a single data source or modality-specific confounding effect.

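### Out-of-bag error is planned as a performance indicator for the random forest, but the earlier univariate screen has already used the out-of-bag patients' response labels, so it will be optimistic

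*Protocol article*

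**What the plan says.** Four statements in the protocol article bear on this.

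- *Preprocessing and feature selection*: "An initial univariate feature-screening step is going to be applied to reduce the feature space". The screen is supervised: "Candidate predictors is going to be tested for their association with the target variable (treatment response category) using appropriate statistical tests". Its result is binding: "Variables not showing evidence of association is going to be excluded from subsequent modelling". It is to be run on the training data only.
- *Machine learning (ML) algorithms*: random forest is the primary approach. For its hyperparameters, "final values are going to be selected according to cross-validated/OOB performance". The forest also carries a comparison of five cumulative feature sets, from clinical and biochemical up to the full set with functional MRI, meant to show what each modality adds. A stricter selection by forest importance follows.
- *Model evaluation and validation*: the models go through nested cross-validation, with selection and tuning confined to the training folds. Forest performance is also to be assessed by OOB error, "which provides an internal estimate of generalisation performance without the need for a separate validation set". OOB errors, overall and per class, are named as performance indicators.
- *Limitations and future directions*: OOB and cross-validation are both said to be possibly optimistic, because the data are complex and come from several centres.

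**The concern.** OOB error estimates generalisation only if the out-of-bag patients had no part in building the model. In this pipeline they did. The screen uses the labels of every training patient, and only then are bootstrap samples drawn from those same patients. A patient who is out of bag for a given tree has still helped to decide which features that tree may use.

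The stated safeguard does not reach this. Confining the screen to a training fold keeps the outer test fold clean, but the OOB samples lie inside the training fold.

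The bias grows with the effective number of candidate features. This matters most for genome-wide methylation, which adds a very large block in a single step. If the modality comparison were read from OOB error, that step could show a large gain with no signal present. The study's stated purpose is to prioritise candidates for later validation, and a false gain of this kind would misdirect it.

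**Working it through.** The article gives no OOB error or AUC, so there is no figure to reproduce. The check is what OOB shows when nothing is predictive.

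**Inputs from the article** (*Sample size calculation*)
- "we required a minimum sample size of 168 subjects with migraine at baseline and 51 controls" and "Moreover, we considered a 6% loss of participants": 168 × 0.94 = 157.9, so 158 patients.
- "Given the rate of >75% response to erenumab observed in randomised clinical trials (30%), as well as the rate of <25% response": read as 30% in each extreme category.
- 47 per group, giving a 94-patient run of the two extremes.

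**Assumptions** (not in the article)
- Screening threshold p<0.05.
- Candidate features: 30 clinical/biochemical, 20 genetic, 1,000 to 10,000 epigenetic, 150 structural MRI, 5,000 functional MRI. Cumulative totals: 30; 50; 1,050 or 10,050; 10,200; 15,200.
- Middle 40% of patients split 20/20 in the four-class run; 50/50 in the binary run.

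**Why the screen leaks.** With 79 patients per class and unit-variance noise, a feature passes if its mean difference exceeds 1.975 × √(2/79) = 1.975 × 0.159 = 0.31 SD in the full sample. About 0.05 × p noise features pass: 0.05 × 10,050 ≈ 503 (512 were kept on average). Each carries a class difference to which the OOB patients themselves contributed. The forest pools these differences and then separates the OOB patients by them.

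**Simulation.** Independent N(0,1) features unrelated to response; F-test screen; class-weighted forest with 300 trees, √p features per split and no tuning; five outer folds; 12 replicates (binary) or 8 (other runs).

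Binary, n=158:

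| Candidate features | OOB AUC (error), screen on all patients | OOB AUC, screen inside each outer training fold | Outer-fold AUC |
|---|---|---|---|
| 30 | 0.54 (0.47) | 0.56 | 0.49 |
| 50 | 0.57 (0.44) | 0.59 | 0.49 |
| 1,050 | 0.85 (0.23) | 0.87 | 0.52 |
| 10,050 | 0.97 (0.10) | 0.97 | 0.52 |
| 10,200 | 0.97 (0.10) | 0.97 | 0.53 |
| 15,200 | 0.96 (0.10) | 0.98 | 0.52 |

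The third column applies the article's own safeguard and is just as biased. OOB AUC with no screen was 0.46-0.51 (run up to 10,200 features), which isolates the screen as the cause.

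**Other settings**
- Four classes, n=158: OOB AUC 0.52, 0.54, 0.77 and 0.87 at 30, 50, 1,050 and 10,050 features. OOB balanced accuracy rose from 0.26 to 0.62, against 0.25 by chance. Outer-fold AUC was 0.50-0.52.
- Two extremes, n=94: OOB AUC 0.56, 0.63, 0.90 and 0.98. Outer-fold AUC was 0.48-0.51.
- Correlated features (binary, n=158, within-block r=0.7, 10 replicates): OOB AUC 0.73 for 1,000 features in 50 blocks, 0.73 for 10,000 in 50 blocks, and 0.82 for 10,000 in 200 blocks. The bias follows effective dimension, not the raw count.

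**The case against.** The strongest reply is that the plan already contains the right estimate. OOB is introduced as an addition to nested cross-validation, and the outer folds stay at chance on noise. The models are labelled exploratory, and the limitations section names OOB as possibly optimistic. The pipeline figure is not shown and the full configuration is deferred to the results paper. The largest inflation needs many independent features, and the planned removal of collinear variables makes the effective number uncertain.

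Much of this stands, and it rules out several stronger readings that a reader might infer:

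- *That the forest is judged on an easier scale than its competitors.* OOB comes on top of nested cross-validation, so the cross-validated metrics apply to the forest too.
- *That tuning on OOB inflates all reported performance.* The text allows cross-validated or OOB tuning. Inside the training folds, a poor criterion can pick a poorer model but does not bias the outer-fold estimate.
- *That the modality comparison will be read from OOB.* The article does not say so; it leaves the source open.
- *That each added modality shows a false gain.* In the simulation the jump came at the epigenetic step and then flattened. With clinical and genetic blocks alone the bias was small.

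What does not stand is the general caveat as an answer. It treats OOB and cross-validation alike and does not name the screen as a cause, whereas here one estimate is sound and the other is not. Nor is this a detail left to a fuller document: the article itself states that OOB estimates generalisation in this pipeline.

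**Conclusion.** The concern holds in limited form. OOB error computed after the supervised screen is optimistic and should not be offered as an estimate of generalisation. The nested cross-validation is unaffected and covers the forest as well.

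The bias is slight with a few dozen candidate features and large once a methylation block of 1,000 or more enters, even with correlated features or four response classes. These sizes depend on the assumed feature counts, threshold and correlation structure; the direction does not. Outer-fold results were computed for the independent-feature runs only, but repeating the screen in each training fold keeps the test fold clean whatever the correlation.

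Two consequences remain. The results paper could carry two conflicting performance figures for the primary algorithm with no rule for which governs. And the five-step modality comparison has no stated source: taken from OOB, it could credit methylation with a gain that is not there.

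**What to change.** Amend the analysis text as follows.

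1. State that random forest performance, and all five modality comparisons, are taken only from the outer folds of the nested cross-validation, with the same metrics as for the other algorithms.
2. Tune the forest in the inner loops, and remove OOB as an alternative tuning criterion.
3. Delete OOB error as a performance indicator, together with the statement that it needs no separate validation set. If it is kept, repeat the univariate screen, and any importance-based selection, within each bootstrap sample so that out-of-bag patients never contribute to it.

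The cost is a few lines of wording, some computing time and less favourable forest figures. No new data are needed. *Status of the study* reports that processing for the stratified analysis is still under way, so the change can be recorded before those results are reported.

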**Figure 3 fig3:**
[figure not shown]
Schematic representation of the machine-learning pipeline applied to the BIOMIGA multimodal dataset.

## Status of the study

The enrolment of participants has been concluded in January 2024. Data cleaning and anonymisation/pseudonymization were completed in July 2024. Data processing for baseline values was completed in May 2025, and baseline data are undergoing the last round of revision from the authors.

Data processing for the analysis of stratified groups is presently ongoing.

## Legal aspects, ethics and dissemination

### BIOMIGA consortium

The BIOMIGA consortium was established within the ERA-Net NEURON programme (Network of European Funding for Neuroscience Research), Joint Transnational Call 2019 “European Research Projects on Biomarkers,” and brings together three complementary centres of excellence in headache research and care: IRCCS Mondino Foundation (Pavia, Italy; coordinating centre), Vall d’Hebron University Hospital (Barcelona, Spain) and the University Medical Centre Hamburg-Eppendorf (Hamburg, Germany). Fundamental research activities commenced on 25 April 2020 and clinical recruitment on 16 June 2020. Recruitment was completed on the 30th of October 2023 and data collection was completed by January 2024. The project ended on 11 September 2024.

A key strength of the consortium is the implementation of harmonised procedures for clinical, radiological and biological data collection across all sites, achieved through a shared, detailed protocol and standard operating procedures, complemented by a training video to ensure correct handling and processing of peripheral blood mononuclear cells.

Overall coordination and scientific leadership were provided by the principal investigator, [name] (IRCCS Mondino Foundation), and local principal investigators at each centre: [name] at Vall d’Hebron University Hospital and [name] at Hamburg University.

### Ethics approval and consent

This study was conducted in accordance with the International Conference on Harmonisation note for guidance on Good Clinical Practice. The Biomiga Protocol received the following approval from each local ethical committee:Pavia Ethical Committee, San Matteo Hospital, n. 20200048923;Ethics committee of the Ärztekammer Hamburg, PV7356;Vall d’Hebron Ethics Committee, AC19/00214.

The study was originally planned to be completed within 3 years; however, due to the COVID-19 pandemic and its impact on clinical and research activities, including restricted access to hospitals and reduced enrolment rates, a 1-year extension was granted by the funding body and duly notified to all relevant Ethics Committees, with no further amendments to the study protocol required.

All participants were fully informed about the study, including the risks and benefits of their participation in the study. Any participant could withdraw from the study at any time, for any reason, specified or unspecified, and without penalty or loss of benefits to which the patient is otherwise entitled. No study-related procedures, including any screening procedures, were performed before the investigator had obtained written informed consent from the participants.

All the information obtained in the study are treated confidentially, complying with the GDPR 2016/679 and the Organic Law of Protection of Personal Data 3/2018, 5th December.

Each participant was assigned a unique patient study number at enrolment. In trial documents, the participant’s identity is coded by study number as assigned at enrolment. The local investigator kept a subject enrolment and identification log that contains the key to the code, that is, a record of the personal identification data linked to each patient study number. This record is filed at the investigational site and can only be accessed by the investigator and the supporting site staff, and by representatives of the sponsor or a regulatory agency for the purpose of monitoring visits or audits and inspections.

### Confidentiality and data storage

The data collected were processed in accordance with the European Union legislation to ensure that requirements regarding personal data protection are met. To ensure a correct management of the data, the Joint Personal Data Management Agreement was elaborated and finally signed on 29 April 2022. Moreover, a Data Management Plan (DMP) was implemented and shared among the partners.

All the records contained in the multimodal dataset have been anonymised or pseudonymised, when full anonymisation was not possible. They have been collected and stored in an online platform created in collaboration with a technological partner, Biomeris (Pavia, Italy) (Figure 4). All partners used the platform to acquire raw clinical, biochemical, and imaging data. Study data were collected and managed using REDCap electronic data capture tools hosted on a Server within the European Union, under the licence hosted by the IRCCS Mondino Foundation. REDCap (Research Electronic Data Capture) is a secure, web-based software platform (44) designed to support data capture for research studies, providing (1) an intuitive interface for validated data capture; (2) audit trails for tracking data manipulation and export procedures; (3) automated export procedures for seamless data downloads to common statistical packages; and (4) procedures for data integration and interoperability with external sources. The REDCap platform facilitated real-time data entry and smooth data sharing. Additionally, the creation and exchange of imaging, genetic, and psychophysical data forms enhanced collaboration and promoted methodological standardisation among consortium members, strengthening the scientific rigour of the project.

**Figure 4 fig4:**
[figure not shown]
Organisation of the informatics infrastructure of the BIOMIGA Project.

### Dissemination

The results are going to be submitted to ClinicalTrials.gov and EudraCT and actively disseminated through peer-reviewed journals, conference presentations, and social media. Moreover, a dedicated web page will be published on the website of the IRCCS Mondino Foundation, available in Italian and English for professional and general public dissemination of the protocol and of the results of this project, as soon as they are available: https://www.mondino.it.

Currently, it is possible to find the entire protocol at https://clinicaltrials.gov/study/NCT04503083.

### Data sharing

The final database using REDCap and an anonymised version is going to be made available via Zenodo^1^ after the publication of the final project’s results, upon written request.

## Discussion

We are entering a new phase in migraine prevention, characterised by the availability of mechanism-based, target-specific therapies. However, the promise of these advances may only be fully realised through a more individualised therapeutic approach in the context of precision medicine, which requires improved patient profiling and reliability of treatment response. CGRP-targeting monoclonal antibodies and gepants are transforming migraine prevention by offering the first mechanism-specific therapies with strong efficacy and good tolerability (7). However, the response to treatment varies significantly, emphasizing the need for biomarkers that can identify which patients are most likely to benefit from modulation of the CGRP pathway.

In parallel, extensive research efforts aimed at identifying biochemical, neuroimaging and genetic biomarkers of migraine have yet to yield markers that are sufficiently robust for routine clinical use in diagnosis, disease stratification or treatment selection. This disconnection between therapeutic innovation and biomarker validation highlights a critical gap in the current precision-medicine paradigm for migraine.

Within this context, the BIOMIGA project was conceived as a multimodal, biomarker-driven study focused on patients treated with erenumab, the first mAB targeting the CGRP pathway to become widely available. By integrating deep clinical phenotyping with molecular, genetic, epigenetic and advanced neuroimaging measures, BIOMIGA is expected to move beyond single-marker approaches and to identify composite biomarker signatures to support a more mechanism-informed and personalised use of CGRP-targeted preventive therapies.

